#### Secondary outcomes

##### Percentage body fat

The percentage body fat will be determined using the InBody body composition analyzer (InBody 770, InBody Co., Seoul, Korea). Participants will be required to stand barefoot on the device and grip the hand electrodes in a standardized posture for measurement. To minimize measurement errors, assessments will be performed with participants wearing light clothing and at least 2 hours postprandially. The InBody 770 provides detailed body composition analysis, including fat mass, lean body mass, and percentage body fat. Results will be automatically calculated and recorded. Duplicate measurements will be taken. If values differ by > 1.0% body fat, a third measurement will be performed and the median recorded [28].

##### Change in muscular strength

The muscular strength will be assessed using handgrip, measured with a digital dynamometer (Takei Physical Fitness Test GRIP-A, T.K.K.5001, Takei Scientific Instruments Co., Ltd., Japan). Participants will stand with their arm by their side without elbow flexion and squeeze the device with maximum effort for 2–3 seconds. Three trials per hand with 10-second of rest between trials will be performed. The highest value either from the right or left hand will be recorded for analysis; the mean of the best right/left trials will be retained for quality control [29, 30].

##### Change in muscular endurance

Static curl-up and prone plank tests will be used to assess muscular endurance [31–33]. In the static curl-up test, participants will assume a curl-up position with the torso flexed at 45°. They will maintain this posture for as long as possible, and the total time (in seconds) sustained in the correct position will be recorded. If the posture is lost for more than 3 seconds, the test will be considered as terminated.

In the prone plank test, participants will support their body on forearms and toes on a mat while maintaining a straight line from head to heels. No floor contact will be allowed other than forearms and toes. Time to failure will be recorded.

##### Change in muscular power

Muscular power will be assessed using two jump-based tests: the vertical jump and the squat jump [34–37]. Both tests will be measured using equipment from Swift Performance Equipment (Queensland, Australia).

For the vertical jump, a Vertec-style jump measurement device will be used. This test consists of a stack of horizontal vanes that can be displaced when touched, allowing direct measurement of maximal reach height. Participants will stand with feet shoulder-width apart and perform a maximal upward jump using both arms and legs to optimize height. Jump height will be calculated as the difference between standing reach height and maximum jump reach. Two trials will be conducted, and the best height (in cm) will be used for analysis.

In the squat jump, a contact mat system will be used to record flight time and calculate jump height using standard kinematic equations. Participants will begin from a static squat position (knee angle 90°, hands on hips, torso upright) and jump vertically without countermovement or arm swing. Two trials will be performed, and the best result will be recorded.

##### Change in cardiorespiratory fitness

Cardiorespiratory fitness will be assessed using the 20-m shuttle run test [38–40]. Participants will run continuously between two markers 20 m apart, guided by audio beeps. The frequency of beeps increases incrementally. The test is terminated if the participant fails to reach the marker twice consecutively or the participant misses the marker three times in total. When the participant can no longer follow the pace, the highest level reached will be used to estimate the maximal oxygen uptake (VO_2_ max).

##### Change in flexibility

Flexibility will be assessed using the sit-and-reach test [41–43]. Participants will sit with their legs fully extended and reach forward along a measuring line while keeping their knees straight. The farthest distance reached will be recorded in centimeters.

##### Change in body mass index

BMI will be calculated by dividing the body mass (kg) by height squared (m^2^). Body mass and height will be measured using a calibrated digital scale and stadiometer (to 0.1 kg and 0.1 cm), with participants barefoot and in light clothing.

##### Change in physical activity

Moderate-to-vigorous physical activity levels will be assessed using the validated Chinese version of the Physical Activity Questionnaire for Older Children (PAQ-C) [44–46]. The questionnaire captures the previous 7 days’ activities; each item is scored 1–5 and averaged to produce a total score. Standard PAQ-C missing-item rules will be applied; questionnaires with > 20% missing will be excluded. This self-report will be used to collect data on physical activity levels.

##### Change in cortisol level

Physical activity interventions have been shown to influence stress regulation and hypothalamic–pituitary–adrenal (HPA) axis function in children and adolescents [47]. Therefore, examining cortisol levels may help explore whether participation in structured exercise programs influences physiological stress regulation in children.

Hair cortisol levels will be used as an indicator of chronic physiological stress and as a psychological marker [48, 49]. A 3-cm segment will be cut from the posterior vertex (20–50 mg) to reflect the prior 3 months of cortisol exposure. Samples will be stored in aluminum foil at room temperature in the dark [50]. Hair washing and cortisol extraction will be performed following a previously established protocol, including isopropanol washing and methanol extraction. Cortisol concentrations will be analyzed using liquid chromatography–tandem mass spectrometry (LC–MS/MS). For internal quality control, 5% of samples will be randomly selected for duplicate analysis to verify reliability [51, 52].

### Sample size

Sample size was calculated based on the primary outcome, MRI-derived MFR, using a repeated-measures analysis including baseline, post-intervention, and 6-month follow-up measurements. The primary endpoint is the between-group difference at the post-intervention assessment (week 16), with the 6-month follow-up included to evaluate maintenance of intervention effects over time.

A power analysis was conducted using G*Power 3.1 (*F* test, repeated-measures ANOVA, within-between interaction; 3 groups × 3 measurements). As no prior randomized controlled trials have examined MRI-derived MFR changes in children following Plyo-HIIT, an effect size specific to MFR is currently unavailable. Therefore, the expected effect size will be estimated based on pediatric exercise intervention studies reporting changes in BMI-related adiposity outcomes, which are conceptually related to body composition adaptations.

A previous study reported a mean between-group difference of 0.2 in BMI *Z* score, with a standard deviation (SD) of 0.45, corresponding to Cohen’s *d* ≈ 0.44 [53]. This was converted to an ANOVA effect size of *f* = 0.22 and used as a conservative proxy for the primary outcome. This approach was adopted to avoid underestimating the required sample size in the absence of directly comparable MFR intervention data.

To adopt a stringent and conservative design strategy, the significance level was set at *α* = 0.01. Statistical power was set at 90% to ensure adequate sensitivity for detecting clinically meaningful intervention effects over time.

Given the 16-week and 6-month follow-ups, a conservative assumption was made for the correlation among repeated measures (*r* = 0.2) to avoid overestimating within-subject stability across extended time intervals. The Greenhouse–Geisser nonsphericity correction was set to *ε* = 0.70, reflecting possible variability and differences between time intervals.

With these assumptions, the analysis indicated that a total of 153 participants is required. To accommodate an estimated 25% attrition rate, the minimum sample size was set at 204. To further ensure adequate power for subgroup and sensitivity analyses, and to allow for potential uneven group sizes after attrition, the recruitment target was rounded up to 210 participants (70 per group).

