## Methods

### Study hypothesis and purpose

This study aimed to investigate the effectiveness of a 16-week school-based Plyo-HIIT intervention in improving MFR among children aged 9–12 years. Specifically, the study compares the outcomes of a Plyo-HIIT program with the SF program and the HE control group. The primary hypothesis is that children allocated to the Plyo-HIIT group will demonstrate greater improvements in MRI-derived MFR compared with the SF and HE groups immediately following the intervention (week 16). The 6-month follow-up assessment (week 42) is included to examine whether intervention effects are maintained over time. In addition, the study will examine intervention-related changes in InBody-derived body fat percentage, muscular strength, endurance and power, cardiorespiratory fitness, flexibility, physical activity levels, body mass index (BMI), and physiological stress, indicated by hair cortisol levels.

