
Participants assigned to the SF group will follow a general structured fitness program aligned with the American College of Sports Medicine and WHO recommendations for youth physical activity. Each session will begin with a 10-minute warm-up that includes jogging and static stretching targeting major muscle groups. This will be followed by approximately 30 minutes of moderate- to high-intensity physical activity, including sport-based games such as basketball, football, and sprinting drills, as well as obstacle courses, dance routines, and basic motor skill drills. The target exercise intensity will be maintained at 60%–80% of age-adjusted maximal heart rate, monitored using Polar heart rate sensors worn by each participant. Sessions will conclude with a 5-minute cooldown involving static stretching and light movement. The first 4 weeks will serve as an adaptation period to gradually introduce participants to structured exercise.

Participants assigned to the HE control group will receive classroom-based health education. Each session will last approximately 45 min and will be delivered by trained researchers in a small-group setting. The course will cover core themes related to physical activity, dietary behaviors, and mental health, incorporating interactive discussions and classroom games to enhance engagement. This group will serve as a non-exercise comparator and will enable the isolation of treatment effects attributable to physical activity.

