### Statistical analysis

All statistical analyses will be performed using SPSS version 28.0 (IBM Corporation, Armonk, NY, USA). Descriptive statistics will be used to summarize baseline participant characteristics in each group. Continuous variables (e.g., age, BMI, percentage body fat) will be presented as means and standard deviations, while categorical variables (e.g., sex, group allocation) will be presented as frequencies and percentages.

The primary outcome measure is the MRI-derived MFR. The primary analysis will focus on the between-group difference in change in MFR at the post-intervention assessment (week 16); this is the primary outcome indicator for the trial. The 6-month follow-up assessment will be included to examine the maintenance of intervention effects over time. Generalized estimating equations (GEE) will be used to account for within-subject correlation across the two post-baseline assessments (post-intervention at 16 weeks and 6-month follow-up). The intervention group will be treated as a three-level categorical variable, with the HE control group as the reference. Time will be specified as a categorical variable. Group, time, and group-by-time interaction will be included in the model. Baseline MFR values, age, and sex will be included as covariates. An exchangeable working correlation structure will be specified, with robust sandwich standard errors used for estimation. Pairwise comparisons will be performed to compare Plyo-HIIT with SF and HE at week 16. Sensitivity analyses using a different working correlation structure will also be performed.

Secondary outcomes, including percentage body fat, muscular strength, muscular endurance, muscular power, cardiorespiratory fitness, flexibility, BMI, physical activity level, and cortisol levels, will be analyzed similarly using a GEE model. For each secondary outcome, the corresponding baseline value will be included as a covariate where appropriate. These analyses will be considered exploratory.

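### The stated 90% power belongs to an omnibus test built on one effect size; it does not carry over to the primary comparison of Plyo-HIIT with SF, an active exercise arm, and that effect size cannot be called conservative there.

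*Protocol article*

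**What the plan says.** The primary hypothesis (Study hypothesis and purpose) is that Plyo-HIIT improves MRI-derived MFR more than both SF and HE at week 16. The Statistical analysis section plans accordingly: "Pairwise comparisons will be performed to compare Plyo-HIIT with SF and HE at week 16". It calls these pairwise comparisons primary and prespecified, and refers back to the Sample size section for their significance level, which is 0.01.

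The two comparators differ in kind. Under Interventions, HE is described as a comparator without exercise. SF has the same two 45-minute sessions a week for 16 weeks and includes "approximately 30 minutes of moderate- to high-intensity physical activity, including sport-based games such as basketball, football, and sprinting drills", at 60%–80% of maximal heart rate.

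The Sample size section uses one effect for the whole trial. Because no MFR effect is available, "the expected effect size will be estimated based on pediatric exercise intervention studies reporting changes in BMI-related adiposity outcomes". The value comes from a previous study with "a mean between-group difference of 0.2 in BMI *Z* score, with a standard deviation (SD) of 0.45", giving d ≈ 0.44 and f = 0.22, "used as a conservative proxy for the primary outcome". The test that was sized is a "repeated-measures ANOVA, within-between interaction; 3 groups × 3 measurements" F test at α = 0.01 with 90% power, r = 0.2 and ε = 0.70. It gives 153 evaluable children, 204 after 25% attrition, and a target of 210 (70 per group). The section gives no expected difference and no power for Plyo-HIIT versus SF.

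**The concern.** If SF has any effect on MFR, the Plyo-HIIT advantage over SF is smaller than its advantage over HE. One effect size cannot then be cautious for both comparators. The only power figure in the article also belongs to a different test from the pairwise comparisons that will decide the primary question.

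The SF comparison is the one that would show something specific to plyometric training, which the abstract's conclusions and the Discussion look for. A reader who takes 90% and the conservative label at face value could read a non-significant SF result as evidence that the two programmes are alike, when the trial may have had little chance of separating them.

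**Working it through.** **1. Reproduce the plan's figure.** Inputs from the Sample size section: k = 3 groups, m = 3 measurements, f = 0.22, α = 0.01, r = 0.2, ε = 0.70.

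- λ = f²·N·m·ε/(1 − r) = 0.0484 × 153 × 3 × 0.70/0.80 = 19.44
- df₁ = (k − 1)(m − 1)ε = 2.8; df₂ = (N − k)(m − 1)ε = 210
- Noncentral F power = 90.0% at N = 153 (89.3% at N = 150)
- Attrition: 153/0.75 = 204

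The stated numbers reproduce, and the 90% is the power of the omnibus interaction.

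**2. Power of the planned contrast.** The week-16 comparison is approximated as a two-arm test adjusted for baseline (noncentral t, two-sided α = 0.01). The article does not state the sidedness of the primary tests, so two-sided is assumed. Let SF achieve a share s of the 0.44 SD effect. The article gives no SF effect, so s is an assumed range.

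- Noncentrality = 0.44(1 − s)/√(1 − r²) × √(n/2)
- Example, s = 0, r = 0.2, n = 51: 0.44/0.980 × 5.05 = 2.27 against a critical value of 2.63, so power is about 37%.

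| r | n per arm | s = 0 | s = 25% | s = 50% |
|---|---|---|---|---|
| 0.2 (plan) | 51 | 37% | 18% | 7% |
| 0.2 (plan) | 70 | 52% | 27% | 10% |
| 0.8 | 51 | 86% | 56% | 23% |
| 0.9 | 51 | 99% | 88% | 47% |

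The 70-per-arm row assumes no attrition. With 70 per arm, r = 0.9 and s = 50%, power is about 65%.

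**3. Detectable difference.** At n = 51, r = 0.2: (2.63 + 0.84) × √(2/51) × 0.980 ≈ 0.67 SD for 80% power. The corresponding figure for 90% is about 0.76 SD. Both exceed the 0.44 SD that was assumed.

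**4. The omnibus test when SF works.** With arm means of 0.44, 0.22 and 0 SD (Plyo-HIIT, SF, HE), f is the standard deviation of the means: √[(0.22² + 0 + 0.22²)/3] = 0.18. Power at N = 153 falls to about 70%. With means of 0.44, 0 and 0, f = 0.207 and power is 85%.

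**5. Separate the two sources of loss.** At s = 0 the comparator contributes nothing, yet pairwise power on the plan's inputs is already 37%. That loss comes from which test was powered, and it applies equally to Plyo-HIIT versus HE. The further fall from 37% to 18% to 7% is specific to SF.

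**The case against.** The strongest reply is that the article never claims 90% for any pairwise contrast. It sizes one omnibus test, and most of the gap between 90% and 37% is a test-mismatch problem. That is right, and the SF-specific part has to be stated as the increment beyond s = 0. The comparator point remains once the test is corrected: 154 per arm would give 90% for d = 0.44 in an unadjusted pairwise test, whereas d = 0.22 would need 615.

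A reader might infer that 90% power against SF is impossible unless SF does nothing. The figures do not support that. On the plan's inputs 90% is missed even when SF does nothing, and at r = 0.9 with 51 per arm power is 88% for a 25% share and 97% for a 10% share. The plan's r = 0.2 was chosen to be low, and a higher correlation between baseline and week-16 MFR is possible.

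The comparator in the cited BMI Z-score study is not stated. That 0.44 is a difference between exercise and no exercise is therefore an assumption, and the true effect on MFR may be larger or smaller. In context, the conservative label concerns the use of a BMI proxy for MFR rather than the choice of comparator. Nor does the article say that both contrasts must succeed, so it cannot be read as making the SF result decisive for the trial.

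Finally, the article already promises estimates with 95% confidence intervals where appropriate and nowhere says that a null SF result means similarity. The misreading is a risk, not a stated intention.

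**Conclusion.** The point holds in a limited form. The calculation is arithmetically sound, but its 90% applies to the omnibus interaction. On the plan's own α and r, the primary Plyo-HIIT versus SF test has about 37% power (51 per arm) to 52% (70 per arm) at the full assumed effect. At SF shares of 25% and 50% it has 18% and 7% with 51 per arm, or 27% and 10% with 70 per arm. The shortfall at the full effect does not depend on what the cited study's comparator was.

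The size depends on the two-sided assumption, the assumed SF shares and the baseline correlation. Across the correlations tried, up to 0.9, a halved effect stays below 90%. A single effect size cannot be conservative against both a non-exercise and an active comparator if SF works at all.

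**What to change.** In the Sample size section, state that the 90% applies to the omnibus interaction only, and do not describe d ≈ 0.44 as conservative for Plyo-HIIT versus SF. Add a separate power statement for that contrast over a stated range of SF effects and baseline correlations, with its detectable difference (about 0.67 SD for 80% power at α = 0.01, 51 per arm, r = 0.2).

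In the Statistical analysis section, state that a non-significant Plyo-HIIT versus SF result will be reported as inconclusive with its confidence interval, not as similarity of the programmes.

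This costs a few sentences and a less favourable stated power. Recruitment and the intervention are complete, but the article places the final outcome analysis after the remaining follow-up, so the wording can still be fixed beforehand. No extra children are needed.

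### N = 153 gives 90% power for f = 0.22, but f = 0.22 is a two-group conversion of d = 0.44 and does not belong in a 3 × 3 interaction test, so the stated power is not the power for the cited effect

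*Protocol article*

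**What the plan says.** The Sample size section of the protocol article sizes the trial with a G*Power F test described as "repeated-measures ANOVA, within-between interaction; 3 groups × 3 measurements". No earlier effect on MRI-derived muscle-to-fat ratio was available, so it borrows one from a previous study: "a mean between-group difference of 0.2 in BMI *Z* score, with a standard deviation (SD) of 0.45", reported as Cohen's d of about 0.44. It continues: "This was converted to an ANOVA effect size of *f* = 0.22 and used as a conservative proxy for the primary outcome". The next sentence says that this approach protects against too small a sample.

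The other inputs are "the significance level was set at *α* = 0.01", "Statistical power was set at 90" percent, "correlation among repeated measures (*r* = 0.2" in the plan's notation, and "nonsphericity correction was set to *ε* = 0.70". The result is that "the analysis indicated that a total of 153 participants is required". This is raised to 204 for 25% attrition and rounded to 210, or 70 per group.

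The section gives no assumed means by group and visit, and does not say whether 0.45 is the SD at one visit or the SD of change. The Statistical analysis section bases the primary analysis on pairwise comparisons of Plyo-HIIT with SF and with HE at week 16, from a baseline-adjusted GEE. For the significance level of these comparisons it refers back to the sample size calculation.

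**The concern.** The conversion rule is not named, but 0.44/2 is exactly 0.22. That rule holds for two equal groups in a one-way comparison. In the within-between interaction test, f is the root mean square of the group-by-time residuals over the nine cells, divided by the SD. Randomisation makes the expected baselines equal, so a 0.44 SD gap after baseline is diluted across groups and visits and yields a much smaller f.

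The effect size in the text and the effect size in the calculation are therefore different quantities, and the 90% belongs only to the second. This is the trial's only power statement. If it stands, readers may take a null result as well-powered evidence against an effect of about 0.44 SD, when the design has much less power for an effect of that size.

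**Working it through.** **Inputs (Sample size section).** k = 3 groups, m = 3 visits, alpha = 0.01, r = 0.2, ε = 0.70, f = 0.22, N = 153, attrition 25%. d = 0.2/0.45 = 0.444, used as 0.44 as in the article.

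**Step 1: reproduce the plan's figure.** G*Power default for this test:
- λ = f²·N·m·ε/(1 − r) = 0.0484 × 153 × 3 × 0.70/0.8 = 19.44
- df1 = (k − 1)(m − 1)ε = 2.8; df2 = (N − k)(m − 1)ε = 210; critical F = 4.00
- Power = 90.04%; at N = 152 it is 89.8%.

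So 153 is reproduced exactly, and 153/0.75 = 204 also matches. The formula was applied correctly, and the default f convention is the one in use.

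**Step 2: the f that d = 0.44 implies.** f = √(mean of squared interaction residuals over the nine cells)/σ, with equal baselines. If only Plyo-HIIT differs, by 0.44σ at both later visits:
- the Plyo-HIIT residuals are −0.196, 0.098, 0.098
- the residuals of each other group are 0.098, −0.049, −0.049
- the squares sum to 0.0860, and √(0.0860/9) = 0.098, that is 0.44 × 2/9.

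If 0.45 is the SD of change, then at r = 0.2 that SD is σ√(2 × 0.8) = 1.265σ, and each f is multiplied by 1.265. The patterns are my assumptions, since the article gives none.

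| Assumed pattern (Plyo-HIIT vs HE = 0.44) | f, single-visit SD | Power at 153 | f, change SD | Power at 153 |
|---|---|---|---|---|
| SF equal to HE, effect sustained or at week 16 only | 0.098 | 16% | 0.124 | 29% |
| SF has half the effect, sustained | 0.085 | 11% | 0.107 | 20% |
| SF has half the effect, half maintained at week 42 | 0.073 | 7% | 0.093 | 13% |

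**Step 3: upper limits.** I searched patterns with equal baselines and group gaps of at most 0.44.
- The largest f is 0.169 (power 62%), or 0.214 (88%) with a change SD. Both need the group difference to reverse sign between week 16 and week 42.
- If time is ignored and f is taken from a three-group one-way layout, it lies between 0.44/√6 = 0.180 and 0.44√2/3 = 0.207 (power 70% to 85%).

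All of these are below 0.22.

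**Step 4: the planned week-16 pairwise comparison.** Assume 51 per arm, two-sided alpha 0.01 and 0.45 as a single-visit SD.
- Unadjusted: noncentrality 0.44√(51/2) = 2.22. Power is 35% (t) or 36% (normal approximation).
- Baseline-adjusted at r = 0.2: 2.22/√(1 − 0.04) = 2.27. Power is 36% (t) or 38% (normal).
- At other correlations (illustrations, not protocol figures): 48–50% at r = 0.5, 69–70% at 0.7, 86–87% at 0.8, 99% at 0.9.
- For 90% at alpha 0.01, about 154 per arm would be needed unadjusted, or 148 adjusted at r = 0.2.

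If 0.45 is instead an SD of change, the adjusted noncentrality at r = 0.2 is 2.22 × 1.265/0.980 = 2.87, and the power is Φ(2.87 − 2.576), about 61%.

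**The case against.** The strongest reply is that nothing was miscalculated: the entered f gives 153 and 90%, and 204 follows. That stands. A reader might infer that the power arithmetic is wrong. It is not; the fault is in the input.

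A second reply is that the article fixes no pattern of means, so the shortfall cannot be stated as one number. That also stands. A reader might conclude that the trial has 16% power, needs 759 children, or can detect only 0.99 SD. Those three figures come from a single pattern in which SF does no better than HE, although SF is an active exercise programme, and from an interaction test that is not the primary analysis. Nor is f = 0.169 a general ceiling: with a change SD, the same extreme pattern gives about 0.214.

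Third, the planned test is a baseline-adjusted week-16 contrast, which has more power than the interaction test and gains from a higher correlation than the deliberately low 0.2. This is fair, but at the plan's own r = 0.2 it does not restore 90% under either reading of the SD.

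Finally, the word conservative may refer to borrowing a BMI z-score effect and not to the conversion. That is a possible reading. But the text attaches the word to the converted f and links it to sample size, and for sample size the conversion works in the other direction.

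**Conclusion.** The concern holds in this form: 90% at N = 153 is correct for f = 0.22 and is not the power for d = 0.44. The direction is firm, because no reading tried reaches 0.22. The size depends on what the article leaves open, namely the SF effect, maintenance at week 42 and the meaning of 0.45, so it is a range:

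- Interaction test: about 7–16% with a single-visit SD, or about 13–29% with a change SD. The most lenient reading, a three-group one-way f, gives 70–85%.
- Planned week-16 contrast at alpha 0.01, r = 0.2 and 51 per arm: about 35–38% with a single-visit SD. It approaches 90% only if the baseline to week-16 correlation is above about 0.8. With a change SD and baseline adjustment it is about 61%.

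The pairwise figures take alpha 0.01 as two-sided and as the level for each comparison, since the Sample size section describes no other adjustment. The documents do not support going further and calling the trial invalid: design, allocation and analysis are untouched, and estimates will be reported with 95% intervals.

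**What to change.** In the Sample size section, withdraw the statement that 153 children give 90% power for d = 0.44. Then do one of two things:

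1. Preferably, report the power or the detectable difference for the two week-16 pairwise comparisons at alpha 0.01 and the achieved N, over a range of baseline to week-16 correlations that includes 0.2.
2. Otherwise, state the assumed means by group and visit, say which SD 0.45 is, derive f from them, and report the resulting power for the interaction test.

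In either case, delete the wording that presents f = 0.22 as a conservative proxy guarding against too small a sample.

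Enrolment should not change. Recruitment and the intervention are complete, and no outcome data are reported in the article, so the restatement can be made before the final analysis. It needs no new participants or data. The only cost is a less favourable stated power.
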